## Abstract

**Background:**

Adolescent Depression Disorder (ADD) is a disease with a high rate of disability and death worldwide, and its incidence is increasing, seriously influencing the physical and mental health of adolescents. Acupuncture is a complementary alternative therapy that has achieved good clinical efficacy in the intervention of depression, but its efficacy in ADD is uncertain. Therefore, the aim of this pilot trial is to preliminarily explore the possibility of acupuncture in the treatment of ADD, and to evaluate the feasibility of conducting further large-scale clinical trials to verify the efficacy of acupuncture.

**Methods:**

In this pilot randomized controlled trial, 60 participants will be randomly assigned to receive acupuncture or sham acupuncture for 8 weeks of treatment and 4 weeks of follow-up. The primary outcome will be the difference in Children’s Depression Rating Scale-revised (CDRS-R) scores at weeks 0 and 8 of treatment. Secondary outcomes will include 17-item Hamilton Depression Scale (HAMD-17) clinical score reduction rate and clinical remission rate, difference in CDRS-R scores, HAMD-17 scores, 14-item Hamilton Depression Scale (HAMD-14) scores, Pittsburgh Sleep Quality Index scale (PSQI) scores, and Columbia-Suicide Severity Rating Scale (C-SSRS) scores. All outcomes will be assessed at weeks 0, 2, 4, 6, 8 of treatment and week 12 of the follow-up period. In addition, we will assess the safety outcomes from baseline to the end of this trial and feasibility outcome after treatment.

**Ethics and dissemination:**

The trial protocol is in accordance with the principles of the Declaration of Helsinki, and has been approved by the Ethics Committee of the Affiliated Traditional Chinese Medicine Hospital, Guangzhou Medical University (approval number 2024NK73). The results of this trial will be made publicly available on the registration platform. Professional writers will not be used for this trial. Future authorship of trial publications will be based on the authors’ contributions.

**Discussion:**

The results of this study will provide information on the efficacy and safety of acupuncture in the treatment of add, and evaluate the feasibility of acupuncture in the treatment of add, which will provide the basis for further clinical intervention and scientific research.

**Clinical Trial Registration:**

http://itmctr.ccebtcm.org.cn/zh-CN/UserPlatform/ProjectView?pid=730cb4d2-3634-4789-a51d-85a20514aa0a, identifier ITMCTR2024000186.

## Background

Depression is a common mental disorder characterized by loss of interest or pleasure, sadness, lack of self-worth, and suicidal tendency (1). Globally, an estimated 5.0% of adults suffer from depression (2), and more than 350 million people are affected by depression (3). Adolescence is a unique period of growth, a stage of sudden physiological, biochemical, endocrine and psychological and behavioral changes, all of which can make adolescents vulnerable to mental health problems. In China, more than 95 million people suffer from depression, with 30.28% of young people under the age of 18 (4). Globally, one in seven adolescents aged 10–19 suffers from a mental disorder, accounting for 13% of the global burden of disease in that age group, and depression is one of the leading causes of illness and disability among adolescents (5). The rise in the incidence of depression among adolescents is particularly worrying since depression is also closely related to suicide, and the suicide rate among adolescents has been on the rise for more than a decade (6). Therefore, ADD have become one of the major public health issues worldwide (7).

Guidelines generally recommend active support and monitoring or psychotherapy for patients with mild depressive disorders, and selective serotonin reuptake inhibitor (SSRI) medications or a combination of psychotherapy and SSRIs for patients with moderate or severe disorders and for patients with mild disorders who do not improve (8). As a recommended treatment, the efficacy of Psychotherapy in ADD is not entirely satisfactory. In a meta-analysis of 366 randomized clinical trials including 36072 patients comparing psychotherapy with control conditions, psychotherapies had lower effect sizes in children and adolescents compared with adults (9). In addition to this, there are many challenges to the widespread use of psychotherapy, including high costs, limited availability of therapists, and insufficient access to treatment. Currently, SSRIs is the recommended first-line pharmacological treatment for ADD (10). However, the choice of SSRIs is also limited. For example, the Food and Drug Administration (FDA) approves only fluoxetine and escitalopram for the treatment of depression in adolescents, but other SSRIs and serotonin–norepinephrine reuptake inhibitors (SNRIs), such as venlafaxine, are commonly used off label for this purpose (6). Long-term use of SSRIs to treat depressive disorders in adolescents may lead to a variety of adverse reactions, including insomnia, nausea or headache, tremors, dry mouth (11), and may even increase the risk of suicidal thoughts and behaviors in adolescents (12). In addition, about 40% of them fail the treatment either with antidepressant medication or evidence‐based psychotherapy (13). Therefore, there is an urgent clinical need for a new treatment for ADD with good efficacy and low side effects.

Acupuncture is currently one of the most popular complementary alternative therapies internationally (14). Accumulating evidence from clinical studies suggests that acupuncture can play a vital role in the treatment of depressive symptoms, with significant reductions in depressive symptoms compared to normal care or psychotherapy alone (15–17), and it is safer and better tolerated than antidepressants alone, with better improvements in quality of life (18, 19). A Meta-analysis (20) showed that acupuncture reduced HAMD scores in adult patients with depressive disorders compared to comfort acupuncture. For ADD, Guideline for adolescent depression in prevention and treatment with integrated Chinese and western medicine suggest that acupuncture may be used for treatment (21). And a study on adolescent depressed rats proved that taVNS is capable of ameliorating adolescent depressive and anxiety like behaviors by regulating plenty of genes in the three brain regions (13). However, there is no clear clinical evidence that acupuncture is effective in ADD, so we designed this pilot trial to preliminarily explore the possibility of acupuncture in the treatment of ADD, and to evaluate the feasibility of conducting further large-scale clinical trials to verify the efficacy of acupuncture.

## Study design and methods

### Study design

This is a single-center randomized controlled trial, and participants will be assigned to receive acupuncture or sham acupuncture in a 1:1 ratio. Each participant will sign an informed consent form prior to enrollment. The protocol followed SPIRIT for TCM statement (22).

The total observation period will be 12 weeks, including an 8-week intervention period (weeks 0-8), and a 4-week follow-up period (weeks 8-12). Assessments will be conducted at baseline, week 2, week 4, week 6, week 8 and week 12. The study process is illustrated in **Figure 1**, while the schedule of enrolment, treatments, and assessments can be seen in **Table 1**.

**Figure 1 f1:**
[figure not shown]
Flowchart of study process.

**Table 1 T1:** .

Time (week)	Baseline	Treatment period				Follow-up
content	0	2	4	6	8	12
Patient Consent Form	✓					
Enrollment Screening Form	✓					
Demographic information	✓					
History of present illness	✓					
Family history	✓					
Past history	✓					
Personal history	✓					
CDRS-R	✓	✓	✓	✓	✓	✓
HAMD-17	✓	✓	✓	✓	✓	✓
HAMA-14	✓	✓	✓	✓	✓	✓
PSQI	✓	✓	✓	✓	✓	✓
C-SSRS	✓	✓	✓	✓	✓	✓
Safety evaluation	✓				✓	
Random form	✓					
Drug combination	✓					
Adverse Event record form	✓					
Serious Adverse Event record form	✓					
Table of trial completion and early termination	✓					
CRF Audit Statement	✓					

### Participants

The researchers will select 60 patients diagnosed with ADD by at least two specialists between October 2024 and July 2025 at the Department of Sleep Psychology, Acupuncture and Encephalopathy of the Affiliated Traditional Chinese Medicine Hospital, Guangzhou Medical University.

### Diagnostic criteria

In the DSM-5, ADD is classified under “depressive disorders”. Therefore, this study will use the DSM-5 diagnostic criteria for depressive disorders as the diagnostic criteria.

### Inclusion criteria

Participants who meet the following inclusion criteria will be included: (1) 12 years ≤ age <18 years; (2) Meet DSM-5 diagnostic criteria for “depressive disorders”; (3) Meet mild to moderate ADD (8≤HAMD-17 score < 20); (4) No suicide risk, “No” to all items on the C-SSRS, and a score <3 on item 3 (suicide) of the HAMD-17; (5) No medication (escitalopram, mirtazapine, etc.) or physiotherapy (transcranial magnetic stimulation, transcranial electrical stimulation, acupuncture, electroconvulsive therapy, etc.) received within the past 1 month; (6) Refuse to take the medication; (7) Good reading and writing ability, and able to communicate normally; (8) Volunteer to participate in this study and sign an informed consent form.

### Exclusion criteria

Participants who meet any of the following criteria will be excluded: (1) Meet the DSM-5 diagnosis for other mental disorders such as bipolar disorder, schizophrenia, post-traumatic stress disorder, and personality disorders currently or previously; (2) With severe or unstable cardiovascular, respiratory, hepatic, renal, hematological or other systemic diseases, as well as acute illnesses, infectious diseases, malignant tumors; (3) Psychoactive substance (e.g., alcohol, drugs, etc.) abuse or dependence history.

### Dropout criteria

Participants who meet any of the following criteria will be considered as dropped out: (1) Self-exit after joining the trial; (2) Lost contact in the middle of the trial for various reasons; (3) Write incomplete or inaccurate clinical information that may affect the results of the trial.

### Removal criteria

Participants who meet any of the following criteria will be removed: (1) Receive a treatment prohibited for this trial; (2) Poor compliance, not completing case observation forms, examinations or treatment as required after inclusion.

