### Statistical analysis

The primary and secondary outcomes of this study will be analyzed using the modified intention to score principle. The other statistical analyses including feasibility outcomes and security outcomes. And the safety analysis will include all patients who have received at least one time of intervention.

Analyses of the primary outcomes will be conducted using linear mixed-effects models (MMRM) and generalized linear mixed models (GLMM) in repeated-measures design, which incorporate the clinical effect rates at weeks 0, 2, 4, 6, 8, and the follow-up period as response variables, as well as baseline values, time with treatment factors, time, and treatment factors as fixed-effects variables for the analyses. This study will assume that missing indicators are randomized, and due to the ability of the MMRM to cope with randomly missing data, this study will not conduct data filling for the primary outcome.

Reliability of our data will be analyzed using Cronbach’s Alpha, which is a commonly used indicator for assessing the internal consistency of a scale (25), and data assessed through the scale are considered reliable only when it is >0.7.

Three sensitivity analyses will be conducted in this study for the primary outcomes. First, the study will exclude missing data and analyzes the complete case dataset. Second, a multiple filling method will be used to fill in the outcomes before conducting the evaluation. Third, the primary outcome will be analyzed based on the set of compliant scenarios. In addition, the study will also conduct subgroup analyses of the primary outcome, which will include gender, age, hospital district, BMI, duration of disease, comorbidities, and medication use. For the analysis of secondary outcome, repeated measures information will also be based on the MMRM method; for other quantitative data outcomes, this study will use the Mann-Whitney U test or t-test, depending on whether the data are normally distributed or not.

Statistical descriptions will be carried out for the adverse reaction indicators, and the method of chi-square test or Fisher’s exact probability will be used to compare the differences between groups.

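### The rules that remove or drop randomised participants are not reconciled with the modified intention-to-treat-type primary analysis, and the article does not say whether those participants are still assessed and analysed

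*Protocol article*

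**What the plan says.** The Removal criteria of the protocol article list two grounds: "Receive a treatment prohibited for this trial" and "Poor compliance, not completing case observation forms, examinations or treatment as required after inclusion". Both arise after randomisation.

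The Dropout criteria list self-exit, loss of contact and a third ground: "Write incomplete or inaccurate clinical information that may affect the results of the trial".

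Under Statistical analysis, the primary and secondary outcomes are to be "analyzed using the modified intention to score principle". This is evidently a translation of modified intention-to-treat. The primary model is an MMRM without imputation, on the assumption stated as "This study will assume that missing indicators are randomized", which reads as missing at random. Complete-case, multiple-imputation and compliant-set analyses are three sensitivity analyses. The safety set is everyone treated at least once.

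Under Feasibility outcomes, completion of at least 80% and drop-out of at most 20% are the thresholds for proceeding.

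**The concern.** Poor attendance, unfinished forms and starting another treatment can all follow from how a participant is responding, and the reasons can differ between real and sham needling. The third dropout ground rests on a judgement about whether the data may affect results. Taking such people out of the comparison, or ending their assessments, no longer compares the groups as randomised.

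The two parts of the article also pull against each other. If the removal criteria take non-compliers out of the primary set, the compliant-set sensitivity analysis largely repeats the primary one. If non-compliers stay in, the removal criteria do not mean what they appear to say. The difference matters in practice, because a week-8 CDRS-R score that is never collected cannot be recovered by any later definition of the analysis set.

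Removal and dropout are also separate classes, so it is unclear whether removed participants enter the completion and drop-out rates on which the decision to proceed depends.

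**Working it through.** **The plan's own figure.** The sample size is 2 × 30 = 60, as stated. The article gives no effect size, SD, power, removal rate or outcome for removed participants. Every size below is therefore an illustration under stated assumptions, with the true effect set to zero and removed participants deleted from the comparison.

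**Precision.** With 30 per arm and a two-sided 5% level (the article gives α = 0.05 without sidedness), the 95% CI half-width is t(58, 0.975) × √(2/30) = 2.00 × 0.258 = 0.52 SD.

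**Bias if removed participants are deleted.** Let f be the share removed in an arm and m the number of SDs by which the removed are worse than the retained. The retained mean then looks better than the full-arm mean by f × m, so

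bias = f₂m₂ − f₁m₁.

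The type I error uses SE = √(1/n₁ + 1/n₂) with n = 30(1 − f).

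| Removed, arm 1 vs arm 2 | m₁, m₂ | Bias (SD) | Two-sided type I error |
|---|---|---|---|
| 10% vs 10% | 0.5, 0.5 | 0 | 0.050 |
| 20% vs 20% | 1, 1 | 0 | 0.050 |
| 10% vs 20% | 0.5, 0.5 | 0.20×0.5 − 0.10×0.5 = 0.05 | 0.054 |
| 10% vs 20% | 1, 1 | 0.20 − 0.10 = 0.10 | 0.065 |
| 10% vs 30% | 0.5, 0.5 | 0.15 − 0.05 = 0.10 | 0.064 |
| 10% vs 30% | 1, 1 | 0.30 − 0.10 = 0.20 | 0.106 |
| 20% vs 20% | 0, 1 | 0.20 − 0 = 0.20 | 0.107 |
| 10% vs 30% | 0, 0 | 0 | 0.050 |

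**Extreme case.** Suppose exactly the worst-responding share q of one arm is removed and the other arm loses people at random. With normal outcomes the shift is φ(z₁₋q)/(1 − q). For q = 0.10 this is 0.195 SD, and for q = 0.20 it is 0.350 SD. The larger is 0.350/0.517, about two thirds of the half-width.

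**Loss of precision.** Deleting 20% per arm (30 to 24) raises the difference detectable with 80% power from (1.96 + 0.84) × √(2/30) = 0.72 SD to (1.96 + 0.84) × √(2/24) = 0.81 SD, even with no bias.

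**Feasibility rates.** As an illustration, let 10% of 60 (6) drop out, a further 20% (12) be removed without completing, and the other 42 complete. If the removed are left out of both rates, completion is 42/48 = 87.5% and drop-out 6/48 = 12.5%, and both say proceed. If they are counted as non-completers and as dropouts, completion is 42/60 = 70% and drop-out 18/60 = 30%, and both say modify. The article does not settle which count applies.

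**The case against.** A reader might infer that removal deletes a participant's earlier scores and ends their visits, so that the intention-to-treat analysis is defeated and the primary comparison is biased. The documents do not support that. The article says only that participants are removed or considered dropped out. It does not say whether they leave treatment, follow-up or the analysis. The compliant-set sensitivity analysis suggests that non-compliers stay in the primary set. If so, the MMRM uses the scores they gave before removal, and bias arises only to the extent that later scores are not missing at random. Nor does the plan promise a full intention-to-treat analysis. What is modified may be defined in an analysis plan that is not shown, and its absence from the article is not the complaint here.

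It would also be wrong to call these two lists the only exclusions. Data management and quality control separately admits only complete, age-consistent and unpatterned questionnaires as valid. That may give the inaccurate-data ground some objective content, although neither section refers to the other. And nothing says that removed participants leave the denominator for completion.

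All of this stands, and it limits the point to an unreconciled rule and a risk. It does not remove the point. Unfinished forms are a data failing, and exit and loss of contact already appear under Dropout criteria, so a separate removal class can readily be read as removal from the trial or its data. Nothing in the article tells staff to go on assessing these participants.

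**Conclusion.** The point holds as a conflict between sections that creates a risk of bias. It does not show that the primary comparison is biased. The removal and dropout rules act on post-randomisation events, and they do not fit a primary analysis that keeps the compliant set for sensitivity.

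The 0.05 to 0.20 SD range rests on assumed removal rates and prognosis, on differences between arms in one or both, and on deletion from the analysis. The 0.35 SD figure is a near-extreme case. The bias is zero when removal and prognosis are equal across arms, or when removal is unrelated to outcome. In a pilot whose results are meant to inform the size of the next trial, and whose completion and drop-out rates decide whether to proceed, the ambiguity deserves correction. It is of moderate weight and does not invalidate the trial.

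**What to change.** Reconcile Dropout criteria, Removal criteria and Statistical analysis by stating that:

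- all randomised participants stay in the primary analysis in their assigned arm;
- CDRS-R collection continues at the scheduled visits through week 12 after poor compliance or prohibited treatment, unless consent is withdrawn;
- the removal criteria define only the compliant set for the third sensitivity analysis;
- incomplete or inaccurate data are resolved by blinded query, not by dropping the participant;
- removed participants count as non-completers in the completion and drop-out rates under Feasibility outcomes.

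These changes concern assessment and analysis only. Whether study treatment goes on after such an event is a clinical matter on which this point takes no position. The cost is protocol wording and a few extra assessments at visits already scheduled.

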### Discontinuation criteria

The trial leader will obtain these interim results and make the final decision to terminate the trial if the following occurs: (1) Participants suffer a severe illness or adverse reaction during the trial; (2) Participants request to discontinue the trial; (3) Participants suffer self-injury, suicidal behavior, or have a change in diagnosis and treatment due to medical condition changes during the trial; (4) Contrary to the purpose and protocol of the study.

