### Security outcomes

The outcomes of safety evaluation will be recorded, including basic vital signs (blood pressure, respiration, pulse, etc.) before and after treatment, and records of adverse events (AEs) during treatment and follow-up.

Classification of AEs: Serious Adverse Events (SAEs) are adverse medical events such as death, life-threatening, permanent or severe disability or loss of function, subjects requiring hospitalization or prolonged hospitalization, and congenital anomalies or birth defects that occur in the course of a clinical trial. Significant adverse events are defined as any occurrence of AEs other than SAEs that result in the use of targeted medical measures (e.g., cessation of needling, symptomatic treatment) and significant abnormalities in hematology or other laboratory tests. An unintended adverse event (UAE) is an AE that is of a different nature, severity, or frequency than the expected risk described in a previous protocol or other relevant information (e.g., investigator’s brochure, drug insert).

Handling of AEs: When a participant has trial-related AEs, including clinically significant abnormalities in laboratory tests, the participant should be assured of appropriate medical treatment, such as stopping the needling, decreasing the frequency, or symptomatic treatment. At the same time, to avoid more serious consequences of the clinical trial, the researcher should decide whether to terminate or suspend the clinical trial in order to protect the rights and safety of the participants.

Recording of AEs: Medical documents related to AE, including request forms for laboratory tests and report forms for test results, should be kept in the original files, and the original records should be kept true, accurate, and complete. All records should be signed and dated by the researcher. The content of AE record includes the name of the AE described in medical terminology, clinical signs/symptoms, start and end time of occurrence, severity, measures taken, and the outcome, etc., and the relevance to the trial protocol should be judged. Measures taken mainly include: no measures taken, adjustment of trial parameters, cessation of needling, combination of medications, hospitalization, or prolongation of hospitalization, etc. AE outcomes are mainly cured, improved, not cured, worsened, died, lost to visit, or unknown.

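### Every participant starts with all C-SSRS answers negative, so a later positive is an emergent harm; the plan should count it by arm as a safety outcome, not only compare mean scores

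*Protocol article*

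**What the plan says.** All references are to the protocol article.

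- **Inclusion criteria, item 4:** "No suicide risk, “No” to all items on the C-SSRS, and a score <3 on item 3 (suicide) of the HAMD-17". Items 5 and 6 restrict entry to patients with "No medication (escitalopram, mirtazapine, etc.) or physiotherapy" in the past month who also "Refuse to take the medication".
- **Study design:** "participants will be assigned to receive acupuncture or sham acupuncture in a 1:1 ratio", with 8 weeks of treatment and 4 weeks of follow-up.
- **Table 1 and Observational indicators and follow-up:** the C-SSRS is given at weeks 0, 2, 4, 6, 8 and 12. Table 1 marks the safety evaluation at weeks 0 and 8 only.
- **Secondary outcomes, item 4:** the C-SSRS appears as a score difference over those weeks, in the same line as the other secondary scales.
- **Statistical analysis:** repeated secondary measures are analysed by MMRM. Adverse reactions are described and compared by chi-square or Fisher's exact test. The safety analysis covers everyone treated at least once.
- **Security outcomes:** the listed content is "including basic vital signs (blood pressure, respiration, pulse, etc.) before and after treatment, and records of adverse events (AEs"), the latter during treatment and follow-up. Neither the C-SSRS nor suicidality is named there or in the SAE definition.
- **Discontinuation criteria:** item 1 is "Participants suffer a severe illness or adverse reaction during the trial" and item 3 is "Participants suffer self-injury, suicidal behavior, or have a change in diagnosis and treatment due to medical condition changes during the trial".
- **Randomization and blinding:** an independent DMC reviews and evaluates the study data.

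**The concern.** The entry rule fixes the baseline of this scale: everyone begins with no positive item. From then on the C-SSRS cannot show improvement. It can only show that some participants have developed ideation or behavior they did not report at entry. That makes it a harm measure, but the plan treats it like the symptom scales, as a mean difference between arms.

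Two things follow. A mean over 30 participants, nearly all at zero, barely responds to a few new positives, and it does not say how many participants were affected. And because the security outcomes do not include the C-SSRS, whether a new positive reaches the safety tables depends on an investigator recording it as an adverse event. New ideation in a depressed adolescent can easily be judged part of the illness and not recorded.

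The participants are adolescents not taking medication, half of them on sham for 8 weeks. The article says the results will provide information on safety, and the pilot is meant to inform a larger trial. The number of participants with emergent ideation or behavior in each arm is a figure that its safety report should carry.

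**Working it through.** The plan gives no figure for suicidality, so there is nothing to reproduce. The check sets the sections side by side and then shows, under stated assumptions, what each summary would reveal.

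**1. Direction of change.** Inclusion item 4 makes each participant's positive-item count zero at entry. Change from entry is therefore zero or worse. If the MMRM for secondary outcomes carries a baseline term, as the model described for the primary outcome does, that term is constant here and adjusts for nothing.

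**2. What the mean shows.** Inputs: 30 per arm (Sample size: 60 participants, allocated 1:1). Assumptions: 3 participants in one arm become positive, each scoring *s* points. The article gives no C-SSRS scoring, so *s* is left free.

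- Shift in arm mean = 3 × *s* / 30 = 0.1 × *s*. With *s* = 1 it is 0.1 point; with *s* = 5 it is 0.5 point.
- If the three positives fall at three different visits with *s* = 1, the shift at each visit is 1/30 = 0.03 point.
- One participant scoring 3 points gives 3/30 = 0.1 point, the same mean as three participants scoring 1 point each. The mean cannot tell 1 affected participant (3.3%) from 3 (10%).

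**3. What the count shows.** The same 3 of 30 is 3/30 = 10%, with an exact (Clopper-Pearson) 95% CI of 2.1% to 26.5%. For 0 of 30 the one-sided 95% upper bound is 1 − 0.05^(1/30) = 9.5%. That bound follows from the sample size and no change of summary improves it. It is a reason to print the interval, so that an empty row is not read as proof of safety.

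**4. Is a case likely to occur?** The article gives no rate, so a range is assumed over 12 weeks. P(at least one case among 60) = 1 − (1 − p)^60.

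| Assumed rate p | P(≥1 case of 60) |
|---|---|
| 2% | 70% |
| 5% | 95% |
| 10% | 99.8% |

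**5. Would a test between arms help?** Normal approximation, 30 per arm, two-sided 5%: power = Φ[(d − 1.96 × SE0) / SE1], where d is the difference, SE0 the pooled and SE1 the unpooled standard error.

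- 5% vs 10%: d = 0.05, SE0 = 0.0680, SE1 = 0.0677; (0.05 − 0.1333)/0.0677 = −1.23; power about 11%.
- 5% vs 20%: d = 0.15, SE0 = 0.0854, SE1 = 0.0832; (0.15 − 0.1674)/0.0832 = −0.21; power about 42%.

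A comparison between arms is therefore weak however it is framed. Counts with intervals are the informative report.

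**The case against.** The best defence is that routes for capture already exist. Adverse events are recorded through follow-up with severity, measures and outcome. The researcher may stop needling or suspend the trial. The DMC's review of study data is not limited to adverse events. Reporting a score difference does not forbid an item-level table, and such tables are often left to an SAP that is not shown. The 3-of-30 example is hypothetical, and the article plans no formal conclusion on safety: its numeric progression criteria concern completion and drop-out. All of this stands. It limits the size of the point, but it does not alter what the article fixes: the C-SSRS is placed among the secondary score differences and outside the security outcomes.

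A reader might infer more, and the document does not support it:

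- *That the entry and stopping rules contradict each other.* They do not. An entry bar stricter than a stopping bar is ordinary design, and the discontinuation section does not interpret C-SSRS answers at all.
- *That emergent ideation meets no stopping criterion.* It meets none by name. But item 1 may apply by judgement, and so may the part of item 3 on a change in diagnosis and treatment.
- *That emergent ideation cannot reach the safety report or the DMC.* What is absent is an explicit link, not a route.
- *That referral or rescue procedures are missing from the trial.* These, and DMC alert rules, are commonly left to a full protocol or charter that is not shown.

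**Conclusion.** The point holds as one about outcome placement and summary measure. The entry rule makes the C-SSRS a one-directional harm measure, and the article fixes a mean difference as its only stated use. Capture of emergent ideation as a safety event is left to discretion.

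The size is illustrative. Three new positives in 30 would be a 10% incidence (2.1% to 26.5%) but a mean shift of only 0.1 point, if each scores one point. At assumed rates of 2% to 10%, the chance that at least one case arises among 60 is 70% to 99.8%. No rate or scoring rule in the document supports a firmer figure. The point affects the quality of safety reporting, not the validity of the primary analysis. It does not show that the trial lacks safeguards or that emergent risk would go unnoticed.

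**What to change.** In Security outcomes, list the C-SSRS as a safety measure. For each arm, report the number and proportion of participants with any treatment-emergent 'Yes' through week 12, ideation and behavior separately, with exact confidence intervals, in the safety population already defined (everyone treated at least once). This can stand in place of the C-SSRS score difference in Secondary outcomes or alongside it. Include these cases in the safety data that the DMC reviews.

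Any action rule for an individual participant is for the investigators and the DMC to set. It should not be added to the Discontinuation criteria as they stand: the trial leader there is to "make the final decision to terminate the trial if the following occurs", so taken literally one positive answer would become a ground for ending the whole trial.

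The cost is some wording and one more safety table from data already collected at every visit. The downside is possibly one secondary outcome fewer.
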